##### Register of critical incidents with the family member with SBD

This register was developed ad hoc for this study. The questions recorded are the following: frequency of suicide attempts in the past six months, number of days of self-harm in the past six months, number of episodes of verbal/physical violence with caregivers in the past six months; frequency of visits to the psychiatric emergency room in the past six months, frequency of therapy sessions conducted out of schedule in the past six months (face-to-face, phone calls, etc.).

##### Family empowerment scale [42]

This scale has a total of 34 items. It is composed of three subscales referring to attitudes, knowledge, and behaviors related to (1) Family, (2) the Service System, and (3) Community Participation. The items are rated on a Likert scale (1-5), where higher scores show greater feelings of empowerment. Both the validity and reliability of this scale are adequate, and the internal consistency of the subscales shows coefficients between α = .87 and α =.88.

##### Depression, anxiety, and stress scale [43, 44]

We have used the short, validated Spanish version with 21 items on the frequency of negative emotional symptoms in the past week. The items are rated on a Likert scale (0-3) where the higher the score, the higher the frequency of symptoms of depression, anxiety, and/or stress. The internal consistency of the scale was excellent, with Cronbach's alphas for the DASS-21 subscales: Depression (α = .94), Anxiety (α = .87) and Stress (α = .91) [45].

##### Difficulties in emotion regulation scale - Spanish version [46]

We used the Spanish validation containing 28 items. This questionnaire is divided into five subscales: (1) Lack of emotional control, (2) Life interference, (3) Emotional inattention, (4) Emotional confusion, and (5) Emotional rejection. The items are rated on a Likert scale (1-5) where higher scores indicate greater difficulty in regulating emotions. Psychometric properties are excellent, with an internal consistency of α = .93 and test-retest reliability of pl = .74, p < .001.

##### Quality of life index-Spanish version [47]

It consists of a 10-item index of perceived quality of life. It refers to physical and emotional well-being, functioning at work, satisfaction with personal relationships and self-independence, support in the community and from an emotional point of view, spiritual well-being, and perceived overall quality of life. The items are rated on a Likert scale (0-10) where higher scores indicate higher perceived quality of life. The psychometric properties are good for both internal consistency (α = .89) and test-retest reliability (r = 0.87).

##### Opinion and Expectations of Treatment Scale

This scale was designed and developed by members of the research team and constructed from an adaptation of another opinion and expectations questionnaire [48]. The constructs this scale assesses are: opinion, acceptance and satisfaction with the skills training program, and the changes in the participants after the completion of each module. The questions refer to the rationale for the intervention, recommendation of the program, satisfaction with the program, usefulness and expectations of the skills training. The items are rated on a Likert-type scale ranging from 0 "Not at all" to 10 "Very much".

##### Qualitative Assessment

After the intervention ends, a focus group will be carried out with 25 participants in order to record family members’ personal opinions about the intervention. A focus group is a qualitative research method that provides information about a specific topic from the perspective of a group of people who share a central element of their experience, reducing the influence of the researcher during the process. In this case, participants will be asked an open question about their willingness to repeat or recommend FC-SBD, and a psychologist will write down each participant's answer.

### Measures - Patients

**Data about demographic variables:** age, sex, educational level, income, employment status, marital status, number/age of children, and history of psychological treatment.Measures of primary outcomes

#### Register of critical incidents with the family member with SBD.

2.Measures of secondary outcomes

##### Interpersonal Needs Questionnaire [49, 50]

We use the Spanish version of this 15-item questionnaire that assesses the degree of dissatisfaction with their need to belong (frustrated belonging) and the degree to which they perceive themselves as a burden to others (perceived burden). The items are rated on a Likert-type scale (1-7) where higher scores indicate higher levels of frustrated belonging and perceived burden to others. Psychometric properties were good: scale reliability was very good (perceived burden, α = 0.96; and frustrated belonging, α = 0.78).

##### Patient Health Questionnaire [51, 52]

It consists of a nine-item questionnaire that assesses depressive symptoms in the past two weeks. The items are rated on a Likert scale (0-3) where higher scores indicate higher frequency of depressive symptoms. The severity of depression on this questionnaire is measured through the total score, which can be categorized as none or minimal, mild, moderate, moderately severe, and severe. Validity has been adequate, with a sensitivity of 88% and a specificity of 88% for major depression.

##### Overall Anxiety Severity and Impairment Scale [53, 54]

We use the Spanish version of this questionnaire, which consists of a five-item instrument that assesses the frequency and intensity of anxiety symptoms in the past week. In addition, it measures interference in work and academic, social, and daily life domains, as well as avoidance behaviors. The items are rated on a Likert-type scale (0-4). The psychometric properties are good in terms of internal consistency (α= 0.86), convergent and discriminant validity, and sensitivity to change (α= 0.86).

##### Validating and Invalidating Responses Scale [55]

It consists of a 16-item scale on the validation and invalidation of family members' responses about their loved ones. It is divided into two subscales (validation and invalidation), and the items are rated on a Likert scale (0-4) where higher scores indicate higher perceived validation or higher perceived invalidation (depending on the subscale).

##### Lum Emotional Availability of Parents [56]

This 15-item questionnaire measures the perceived emotional availability of primary caregivers. The items are rated on a Likert scale (1-6) where higher scores indicate greater emotional availability of caregivers. Psychometric properties were excellent for both subscales (mother, α = .9; and father, α = .93). In addition, test-retest reliability was also adequate for the mother's subscale (r = .92) and the father's subscale (r = .85).

### Data analyses

Regarding data analysis, the CONSORT guidelines [57] will be followed. First, participants' scores in the two conditions before receiving the intervention will be compared to check that there are no significant differences between them on the outcome measures and that they are, therefore, comparable after randomization. ANOVAs will be conducted for continuous variables and Chi-square tests for categorical variables. For outcome measures at post-treatment, we will study whether the assumption of homoscedasticity is met with Leven's test. If this assumption is met, repeated-measures MANOVAs and F-tests will be used to compare the two experimental conditions. If the homoscedasticity assumption is not met, the Brown-Forsythe test will be applied. F-tests for statistical significance will be followed by post hoc comparisons. In particular, Tukey will be used when the homoscedasticity assumption is met, and Games-Howell if the homoscedasticity assumption is not met. Appropriate analyses will also be carried out to calculate intervention effect sizes and confidence intervals. The intention-to-treat principle will be used when analyzing pre- and post-treatment data and at six-month follow-up, using mixed-effects models with full information and maximum likelihood estimation. This method has been recommended due to its flexibility in handling missing data [58]. To complement the MANOVA results and post hoc comparisons, effect sizes will be calculated using the standardized mean difference proposed by Cohen [59]. These effect sizes will be calculated to assess changes within and between groups, all based on a pooled standard deviation. Although per-protocol analyses (only analyses of data from participants who complete treatment) suffer from selection bias, they will also be conducted because they allow conclusions to be drawn about the maximum efficacy of the intervention in participants who are fully compliant with treatment. However, when the trial is over, the analytical methodology for controlled clinical trials will be reviewed before analyzing the data to select the most appropriate analytical procedures.

For the qualitative study, semi-structured, in-depth interviews will be used. These interviews will follow the guidelines of Knox and Burkard [60]. The research design will be carried out following the criteria established by Cooke, Smith and Booth [61]. Data will be analyzed using the consensual qualitative research (CQR) method. This methodology has been developed by clinical psychologists to specifically investigate the experience of individuals undergoing psychological treatment [62]. Data reporting will be carried out following the COREQ guidelines [63]. Furthermore, we will attempt to meet the criteria for quality in qualitative research recently developed by Levitt et al. [64] in order to pursue what the authors refer to as methodological integrity in the qualitative field.

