**Methods:**

The study design consists of a two-arm randomized controlled trial with two conditions: FC-SBD or Treatment as usual optimized (TAU-O). Participants will be relatives of patients who meet DSM-5 criteria for SBD. The caregivers` primary outcome measures will be the BAS. Secondary outcomes will be DASS-21, FES, DERS, QoL. The patient’s primary outcome measures will be the frequency of critical incidents with the family member with SBD. Secondary measures will be the INQ, PHQ-9, OASIS. Participants will be assessed at pretreatment, post-treatment, and 6-month follow-up. The intention-to-treat principle will be used when analyzing the data.

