### Sample size

The sample size for this study was generated from effect sizes found in other studies with relatives of people with mental disorders. In the literature, we found a controlled study by Grenyer et al. [22] on a psychoeducational group intervention protocol for family members of people with borderline personality disorder. On the one hand, they found medium to large effect sizes for dyadic adjustment (d=0.78) and family empowerment (d=1.4); on the other hand, they found medium effect sizes for burden (d=0.45) at post-test and 12-month follow-up. The results of these effect sizes are consistent with other studies on psychological treatments for other mental disorders, such as a meta-analysis by Baruch, Pistrang and Barker [34] on psychological interventions for bipolar disorder (Burden, g = -.80). Based on the results of these studies, we expect an effect size of 0.60 because the design of this study consists of two experimental groups. For the calculation of the sample size, we used the G*Power 3.1 software [35], taking into account an alpha of 0.05 and a statistical power of 0.80 in a two-tailed t-test. We need a sample size of 90 participants (45 relatives per condition) to reach an effect size of 0.60 for burden. Finally, we considered possible sample loss during the treatment program. Based on studies of interventions for relatives of people with borderline personality disorder, we expect a 30% dropout rate [17, 23, 27, 36, 37]. Therefore, taking this outcome into account, our study requires a total sample size of 124 participants (62 participants per experimental condition).

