### Measures - Relatives (participants)

**Data on demographic variables**: age, sex, educational level, income, marital status, number/age of children, and history of psychological treatment.1. Measures of primary outcomes

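### Non-significant baseline tests cannot show that the randomised arms are comparable; describe baseline without tests and adjust each outcome for its own baseline value

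*Protocol article*

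**What the plan says.** The Data analyses section opens with a comparison of the two arms before treatment, done "to check that there are no significant differences between them on the outcome measures and that they are, therefore, comparable after randomization". The tests are named: "ANOVAs will be conducted for continuous variables and Chi-square tests for categorical variables". The section gives no significance level for them, no list of the scores to be tested, no allowance for the number of tests, and no action if one is significant.

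For efficacy, the same section names repeated-measures MANOVAs with F-tests, or a Brown-Forsythe test if variances differ. It also names mixed-effects models over the pre-treatment, post-treatment and six-month data for the intention-to-treat analysis, and standardised mean differences within and between groups. Baseline enters these models as one of the time points. Neither a baseline covariate nor a common baseline mean for the two arms is named. The closing sentence leaves the final choice of methods to a review once the trial has ended.

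The relatives' primary outcome is burden (abstract: "primary outcome measures will be the BAS"). The Sample size section says: "We need a sample size of 90 participants (45 relatives per condition) to reach an effect size of 0.60 for burden". It raises the number to 62 per arm, 124 in total, for dropout.

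**The concern.** The plan reads a non-significant test as evidence of balance, which fails in two ways. First, allocation is by random number software run by someone outside the team, so any baseline difference is chance by design and the test asks a question whose answer is known. Second, failing to reject is not evidence of equality. The p-value depends on sample size, whereas the effect of an imbalance on the result depends on how strongly the baseline score predicts the outcome.

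The practical stake is that an imbalance in burden can pass the check while the planned comparison does nothing to condition on it. Because baseline values are collected anyway, conditioning on them costs nothing and makes the estimate more precise.

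**Working it through.** **The plan's own figure.** With d = 0.60, "taking into account an alpha of 0.05 and a statistical power of 0.80 in a two-tailed t-test", the noncentral t calculation gives 45 per arm (power 0.804), so the stated 90 reproduces. The baseline check applies to everyone randomised, so n = 62 per arm below.

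**Largest difference that passes.** In SD units, with 0.05 per test assumed:
- t(0.975, 122) × √(2/62) = 1.98 × 0.180 = 0.356 SD.

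**How often imbalances of this kind arise by chance.** The standard error of the standardised baseline difference is √(2/62) = 0.180.
- An absolute imbalance of 0.356 SD or more: 5% of randomisations, by construction.
- Median absolute imbalance: 0.674 × 0.180 = 0.12 SD.
- Above 0.20 SD but still non-significant: about 22%.

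**Chance of at least one significant result under correct randomisation.** For k independent tests it is 1 − 0.95^k; correlated cases were simulated with equal correlation among the scores.
- Six whole relatives' measures (BAS, incident register, FES, DASS-21, DERS, quality of life): 26% if independent; 24%, 21% and 16% at correlation 0.3, 0.5 and 0.7.
- Eighteen relatives' scores (BAS 1, register items 5, FES subscales 3, DASS-21 subscales 3, DERS subscales 5, quality of life 1): 60% if independent; 51% and 40% at correlation 0.3 and 0.5.

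The range is therefore about 16% to 60%. It treats relatives as independent. Relatives of one patient are randomised together, and an ANOVA that ignores this would raise the rate. For example, an assumed design effect of 1.15 turns 0.05 per test into 0.068, and six independent tests then give 34%.

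**Shift in the burden estimate.** Let δ be the baseline imbalance and r the baseline-to-post correlation, with equal SDs at both times. The documents do not give r; 0.3 to 0.7 is assumed. A post-score contrast moves by rδ. A change-score or group-by-time contrast moves by (1 − r)δ in the opposite direction.

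| r | post-score, δ = 0.356 | change, δ = 0.356 |
|---|---|---|
| 0.3 | 0.11 SD | 0.25 SD |
| 0.5 | 0.18 SD | 0.18 SD |
| 0.7 | 0.25 SD | 0.11 SD |

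Against 0.60 these shifts are 18% to 41%. At the median imbalance and r = 0.5 the shift is 0.12 × 0.5 = 0.06 SD, or 10% of 0.60.

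**Gain from adjustment.** The variance of the treatment contrast is proportional to 2(1 − r) for change scores and to 1 − r² after baseline adjustment. The ratio is (1 − r²) / [2(1 − r)] = (1 + r)/2. This is 0.65, 0.75 and 0.85 at r = 0.3, 0.5 and 0.7, a reduction of 35%, 25% and 15%.

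**The case against.** The strongest reply is that the check is inert. No covariate, model or exclusion depends on its result, so a false alarm triggers nothing pre-specified, and deleting the tests alone would leave every efficacy result unchanged. That stands. The gain comes from the second half of the fix, the adjustment.

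A second reply is that baseline is already in the modelled data. This is true, but a group-by-time contrast subtracts the baseline in full and does not condition on it, so it behaves like a change score. The reply does limit the post-score column above: that column applies to a between-group effect size computed at post-treatment, not to the MANOVA.

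A third is that covariates are often left to the analysis plan or full protocol, and that the section calls its methods open to review. Silence on a covariate is therefore not the fault here. The fault is the stated inference, made alongside named analyses that do not condition on baseline.

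Two stronger readings are tempting:
- A reader might infer that false alarms are bound to occur in around half of such trials. The article fixes neither the list of scores nor the level, and six correlated measures give as little as 16%. Adding patients' scores or demographic items would raise the figure, but the text does not say that these are tested.
- A reader might infer that the burden result will be biased, or moved by about 30%. Chance imbalance averages out over randomisations, and that size of shift needs a roughly 1-in-20 imbalance together with an assumed r of 0.5.

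**Conclusion.** The concern holds as a free improvement. Comparability cannot be inferred from non-significant baseline tests: a difference of up to 0.36 SD passes at 62 per arm. The consequence is limited to the precision and the single estimate of this trial. The shift in burden is typically about 0.06 SD (median imbalance, r = 0.5), and 0.11 to 0.25 SD at the extreme that still passes, against a planned 0.60. The randomised comparison is not biased on average, and the sample size calculation is unaffected. These figures rest on 0.05 per baseline test, r between 0.3 and 0.7, equal SDs at both times and independent relatives; the article states none of these for this purpose.

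**What to change.** Remove the baseline ANOVAs and chi-square tests, together with the inference that the arms are comparable. Present baseline means, SDs and counts by arm without p-values. Pre-specify that every efficacy contrast adjusts for the baseline value of that outcome, whatever the observed balance, either as a covariate or through a mixed model that constrains the arms to a common baseline mean. Settle this before the data are analysed, so that the later review of methods does not reopen it.

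The cost is a change of wording. No further data or participants are needed. Compared with a change-score or group-by-time contrast, the variance falls by, for example, 25% at r = 0.5.

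### The planned burden comparison takes the pre-treatment BAS score as a response and names no adjustment for it; adjusting would be at least as precise and costs only wording

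*Protocol article*

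**What the plan says.** The Abstract names the primary outcome and the visits: "The caregivers` primary outcome measures will be the BAS" and "Participants will be assessed at pretreatment, post-treatment, and 6-month follow-up".

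The Sample size section sets the calculation "taking into account an alpha of 0.05 and a statistical power of 0.80 in a two-tailed t-test". The effect is given as "we expect an effect size of 0.60 because the design of this study consists of two experimental groups", and the result as "We need a sample size of 90 participants (45 relatives per condition) to reach an effect size of 0.60 for burden".

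The Data analyses section then gives the efficacy tests: "If this assumption is met, repeated-measures MANOVAs and F-tests will be used to compare the two experimental conditions". It also plans mixed-effects models, fitted by maximum likelihood, for the intention-to-treat analysis of all three visits. Its only other stated use of the pre-treatment scores is a significance check that the arms are comparable. It does not say whether the efficacy test is the condition main effect, the condition-by-time interaction or a contrast at one visit. It does not say how the mixed model handles baseline. It ends by leaving the choice of procedures open to review before the data are analysed.

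**The concern.** In a repeated-measures analysis of these visits, the pre-treatment score sits on the outcome side of the model. Randomisation makes the expected difference at that visit zero. The consequence depends on the term tested:

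- The **condition main effect** averages the null visit in with the others, so the estimated effect is diluted.
- The **condition-by-time** term compares changes from baseline. It subtracts the whole baseline score, whatever its correlation with the later score, and so carries more noise than an adjusted comparison.

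A contrast that conditions on baseline avoids both losses. It also removes the effect of a chance baseline imbalance from the estimate. The section shows interest in such imbalance by testing for it, but names no use of the result. What is at stake is precision on the primary outcome, from a score that is already collected before the intervention.

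**Working it through.** **Inputs from the documents.** Two-sided alpha 0.05, standardised effect 0.60 (so SD = 1), 45 evaluable relatives per arm (Sample size); three visits (Abstract).

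**Assumptions.** The documents give no correlation between visits. I take one common r for every pair of visits and show 0.3, 0.5 and 0.7. Relatives are treated as independent. The effect is 0 at baseline and 0.60 SD at both later visits.

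**The protocol's own figure.** For a two-sample t-test the noncentrality is 0.60 × √(45/2) = 2.85 on 88 df. Exact power is 80.4% with 45 per arm and 79.5% with 44, so 45 is the smallest sufficient number and the stated 90 reproduces.

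**Effective standardised effects.**

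- Condition-by-time, pre to post (change score): a change has variance 2(1 − r), so d = 0.60/√(2(1 − r)).
- Condition main effect over three visits: the mean difference is (0 + 0.60 + 0.60)/3 = 0.40 and the mean of three scores has variance (1 + 2r)/3, so d = 0.40/√((1 + 2r)/3).
- Post-treatment contrast adjusted for baseline: residual variance is 1 − r², so d = 0.60/√(1 − r²).

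Each d is put into the same noncentral t calculation with 45 per arm:

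| Test | r = 0.3 | r = 0.5 | r = 0.7 |
|---|---|---|---|
| Change score: d | 0.507 | 0.600 | 0.775 |
| Change score: power | 66.2% | 80.4% | 95.3% |
| Main effect, three visits: d | 0.548 | 0.490 | 0.447 |
| Main effect, three visits: power | 72.9% | 63.2% | 55.5% |
| Baseline-adjusted: d | 0.629 | 0.693 | 0.840 |
| Baseline-adjusted: power | 83.9% | 90.2% | 97.6% |

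**Variance ratio.** Adjusted over change score is (1 − r²)/(2(1 − r)) = (1 + r)/2, that is 0.65, 0.75 and 0.85. The adjusted contrast has 35%, 25% and 15% less variance, and less at every r below 1. Against the single-visit t-test the ratio is 1 − r², so adjustment loses nothing there apart from about one degree of freedom.

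**Variant.** If condition-by-time is tested over all three visits on 2 df, power is 68.5%, 83.2% and 97.0% when the effect is fully kept at six months. It is 55.2%, 70.7% and 90.9% when the effect is halved by then.

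**The case against.** A reader might infer that the trial's real power is only 56–73%, or that the stated 80% is wrong. The documents support neither.

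- The 56–73% range belongs to the condition main effect over three visits, and no sentence names that term as the efficacy test. Hypothesis (a) in the Background expects larger gains under FC-SBD than under TAU-O. That is differential change, so condition-by-time. On that reading the pre-post test falls below 80% only when r is under 0.5.
- The Sample size section says openly that its figure is for a t-test, and the figure reproduces. Sizing a trial on a simple test and analysing it with a longitudinal model is common practice.
- One cannot say that the plan rejects adjustment. The baseline handling of the mixed model is not stated, and a model with a common baseline mean would act like ANCOVA. An article commonly leaves such detail to an analysis plan, and none is shown here.
- The gain may be small. The BAS looks back six months and the FC-SBD programme lasts three, so the pre- and post-treatment recall periods overlap, which would tend to raise r. At r = 0.7 adjustment adds about two points over the change score (97.6% against 95.3%).
- The Study design section randomises relatives of one patient together, so every power figure above is optimistic where such groups occur.

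All of this stands, and it limits the point to efficiency. It does not remove it: the tests that the article does name put baseline among the responses, and adjustment is at least as precise as a change-score or an unadjusted single-visit comparison.

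**Conclusion.** The point holds as a free improvement in precision. It is not an error in the sample-size calculation.

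Under the assumptions above, a baseline-adjusted post-treatment contrast has 84%, 90% and 98% power at r = 0.3, 0.5 and 0.7. The pre-post condition-by-time test has 66%, 80% and 95%, and the three-visit condition main effect 73%, 63% and 56%. The gain over the change score is therefore about 18, 10 and 2 percentage points (83.9 − 66.2, 90.2 − 80.4, 97.6 − 95.3). The absolute levels depend on r, on independent relatives and on the full 0.60 SD effect being present. The variance advantage over the change score, (1 + r)/2, depends on r and on equal variances at the two visits, not on the size of the effect.

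**What to change.** In the Data analyses section:

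- State that the efficacy contrast for the BAS is the FC-SBD minus TAU-O difference after treatment, adjusted for baseline BAS. Name the visit; the power figures here use post-treatment.
- Obtain it by ANCOVA, or by the mixed model already planned, with baseline either as a covariate or as a response whose mean is constrained to be equal in the two arms.
- State that the condition main effect averaged over a baseline visit is not the efficacy test.
- Treat each secondary scale in the same way, with its own baseline.

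The Sample size calculation need not change for this point. The cost is wording only: no new data and no further participants, since the baseline scores are already part of the assessment schedule.

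### A Levene pre-test on post-treatment scores chooses between a repeated-measures comparison and a Brown-Forsythe test that ignores baseline, and no single primary analysis of burden is fixed

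*Protocol article*

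**What the plan says.** Under Data analyses the protocol article states that, for outcomes at post-treatment, "we will study whether the assumption of homoscedasticity is met" by Levene's test. If it is met, the two conditions are compared by repeated-measures MANOVA and F-tests. If not, "If the homoscedasticity assumption is not met, the Brown-Forsythe test will be applied". The post hoc procedure switches in the same way, between Tukey and Games-Howell.

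For the relatives, the "primary outcome measures will be the BAS" (abstract, Methods), so burden falls under this rule.

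The same section also plans intention-to-treat mixed-effects models, fitted by maximum likelihood to the pre-treatment, post-treatment and six-month data. No variance pre-test governs these. The section does not say which route is primary. It presents the effect sizes as a complement to the MANOVA results, and it leaves the choice of methods open to review once the trial has ended.

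The sample size section plans the burden comparison "taking into account an alpha of 0.05 and a statistical power of 0.80 in a two-tailed t-test" and concludes: "We need a sample size of 90 participants (45 relatives per condition) to reach an effect size of 0.60 for burden".

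**The concern.** The fallback is not the repeated-measures test made robust to unequal variances. The Brown-Forsythe test of means compares independent groups and has no time factor. With two arms it reduces to the Welch t-test, so a failed Levene test discards the pre-treatment score. The article does not use the word one-way. That reading follows from what the test is and from its pairing with Games-Howell, which is also an independent-groups procedure.

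Unequal variance is a reason to change the standard error, not to drop the baseline. Under this rule, whether baseline is used for burden, or for any secondary outcome, turns on a variance test that is unreliable at this sample size. At stake are power, the treatment of chance baseline imbalance, and consistency across outcomes within one trial.

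**Working it through.** **Inputs from the document.** Two-sided alpha 0.05, power 0.80, t-test, d = 0.60 for burden, 45 evaluable relatives per arm (Sample size). Effect sizes are based on a pooled SD (Data analyses).

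**Assumed, not in the document.** Pre-post correlation r = 0.3, 0.5, 0.7. Ratio k of the FC-SBD to the TAU-O post-treatment SD = 1.0, 1.3, 1.5.

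**1. The plan's own figure.** Exact noncentral-t power at d = 0.60 is 0.795 with 44 per arm and 0.804 with 45. So 45 per arm (90) reproduces.

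**2. Precision of each branch.** With equal SDs (σ) and two visits, the variance per person behind the arm contrast is:
- change score (the group-by-time F-test): 2(1 − r)σ²
- post score only (Welch): σ²
- post score adjusted for baseline: (1 − r²)σ²

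In that order, in units of σ²:
- r = 0.3: 1.40, 1.00, 0.91
- r = 0.5: 1.00, 1.00, 0.75
- r = 0.7: 0.60, 1.00, 0.51

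The change test beats the post-only test only when r exceeds 0.5. Baseline adjustment is the most precise of the three at each of these correlations.

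**3. Simulation.** Normal data, 45 per arm, at least 20,000 trials per setting. The pre-treatment SD and the TAU-O post-treatment SD are 1, and the FC-SBD post-treatment SD is k. To keep pooled d at 0.60, the arm difference is 0.60 × √((1 + k²)/2), which is 0.600, 0.696 and 0.765 for k = 1.0, 1.3 and 1.5. Mean-centred Levene at 5% on post scores selects the change test if it does not reject and Welch on post scores if it does. The fixed comparator is analysis of covariance on the post score with baseline as covariate. Power is in percent, to within about one point:

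| r | k | Change test always | Welch on post always | Gated rule | Fixed, baseline-adjusted |
|---|---|---|---|---|---|
| 0.3 | 1.0 | 67 | 80 | 67 | 83 |
| 0.3 | 1.3 | 71 | 80 | 75 | 83 |
| 0.3 | 1.5 | 74 | 80 | 78 | 83 |
| 0.5 | 1.0 | 81 | 81 | 81 | 90 |
| 0.5 | 1.3 | 85 | 80 | 83 | 90 |
| 0.5 | 1.5 | 87 | 80 | 82 | 90 |
| 0.7 | 1.0 | 95 | 81 | 94 | 97 |
| 0.7 | 1.3 | 97 | 80 | 90 | 97 |
| 0.7 | 1.5 | 97 | 80 | 85 | 97 |

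**4. What the gate does.**
- Levene rejects in about 5%, 36% and 69% of trials at k = 1.0, 1.3 and 1.5.
- The gated verdict differs from that of always testing change in about 1%, 7–8% and 12–13% of trials at those ratios.
- With no treatment effect, the gated rule rejects in 4.6% to 5.2% of trials.
- The mean arm difference is 0.60 pooled SDs whether computed on change or on post scores.

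**The case against.** The strongest reply is that the intention-to-treat mixed model escapes the gate, so Levene does not decide every comparison of burden. That is correct, and it limits the point to the MANOVA and F-test route. It does not remove the point: with no stated hierarchy, the gated result could be reported as the main one.

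A reader might infer several stronger things that the document does not support:

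- **That the branches have different estimands.** Randomization makes the baseline means equal in expectation, so for a pre-post comparison the arm difference in change and in post scores is the same quantity. A joint test over three visits would differ from a post-only test, but that was not examined here.
- **That the raw disagreement between the two tests measures the harm.** At pooled d = 0.60 they disagree in 17% to 27% of trials when both are run on every dataset, and they do so even with equal SDs. The gate's own effect is the smaller figure in step 4. Fixing the difference at 0.60 TAU-O SDs instead lowers the pooled d (0.60/1.160 = 0.52 at k = 1.3), which is not the planned effect.
- **That type I error is inflated.** It is not, with equal arms.
- **That Levene fails most often when FC-SBD works.** This is plausible, but the document gives no variance data.

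It is also fair to say that the gate is not always worse than testing change. At k = 1.3 it gains about 4 points at r = 0.3 and loses about 7 at r = 0.7. The lack of a check on covariance matrices across visits is detail that an article may leave to the analysis plan, and it is not part of this point.

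**Conclusion.** The point holds as a stated rule that is poorly chosen and cheap to replace. It does not invalidate the trial's error control. Over the assumed range, the gated rule has 67% to 94% power against 83% to 97% for one fixed baseline-adjusted analysis. The gap runs from about 3 points (97 − 94, at r = 0.7 and k = 1.0) to about 16 (83 − 67, at r = 0.3 and k = 1.0), and the fixed analysis is better in all nine settings. Whether the gate helps or hurts relative to always testing change depends on a correlation that the document does not give.

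The figures rest on normal data, 45 evaluable relatives per arm, two visits, independent relatives, and the independent-groups reading of Brown-Forsythe.

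**What to change.** Delete the Levene step and the Brown-Forsythe branch, together with the post hoc switch that hangs on them. With two arms, no post hoc comparison between arms is needed.

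Name the intention-to-treat mixed model already planned as the single primary analysis for burden, and use the same model for the other continuous outcomes. Specify:
- adjustment for baseline, or baseline means constrained equal across arms. Without this, a group-by-time contrast on complete pre-post data gives back the less precise change comparison;
- an unstructured covariance across visits, with variances allowed to differ by arm, or robust standard errors;
- the arm contrast at each visit, post-treatment and six months.

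This deals with unequal variances without a pre-test. The cost is a change of wording and a few extra variance parameters. No new data are needed and the sample size does not change.
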